#### Study hypotheses

There are two hypotheses, one related to the primary clinical effectiveness outcome (OASI rates) and one to the primary implementation outcome (OASI-CB adoption):
The OASI rate will decrease in all study arms following the implementation of OASI-CB. There will be a significant difference in reduction of OASI rates between units in the peer support and lean implementation arms, such that the reduction in OASI rates will be higher in the peer support arm as compared with the reduction in OASI rates in the lean implementation arm.There will be a significant difference in care bundle adoption between units in the peer support and lean implementation arms, such that the levels of adoption will be higher in the peer support arm.

#### Sample size and power

The sample size calculation aimed to identify the minimum number of clusters (maternity units) required to provide a study power of at least 0.80 with a statistical significance level of 0.05 to detect a 0.5% difference in OASI rates between the peer support and lean implementation arms following the implementation of OASI-CB.

The OASI rate is 3.5% according to the National Maternity and Perinatal Audit (NMPA) [5]. The units in the peer-support arm are expected to achieve a similar rate of reduction in OASI rates as the relative reduction of 20% observed in OASI1, or in absolute terms a reduction in OASI rates from 3.5% to 2.8%. We assume that the relative reduction in the lean implementation arm will be only 5%, or in absolute terms a reduction in OASI rates from 3.5% to 3.3%.

Using the Shiny CRT Calculator [26] by Hemming et al. and a trial design that includes baseline measures, a cross-sectional sampling, an exchangeable correlation structure, a cluster size of 3600 (average maternity unit size according to NMPA), allowance for a varying cluster sizes (coefficient of variation 0.4 according to the NMPA), and an intraclass correlation of 0.007 (according to OASI1), the minimum number of clusters would detect the assumed difference in OASI after implementation of the OASI-CB is ten; therefore, the study will have ten units in each trial arm.

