### Clinical effectiveness evaluation

#### Data collection and management

The clinical effectiveness of the OASI-CB is evaluated through its impact on perineal outcomes in women across all participating units. As OASI is an acute pregnancy outcome, women may receive the four elements of the bundle as they become eligible, dependent on whether the attending clinician (midwife or obstetrician) chooses to, or is trained to use the care bundle. Women are not randomised to receive the care bundle. All women who have a vaginal birth (spontaneous or assisted) are eligible to receive the OASI-CB, unless they do not consent to one of the elements of the care bundle or are in a birthing position that makes it unfeasible to implement all elements of the care bundle (e.g. water birth).

Individual woman-level data will be extracted from local electronic Maternity Information Systems (MIS) for all participating units in England, Scotland and Wales. The MIS data extract will include demographic and clinical information related to primary and secondary clinical outcomes, as well as a small set of variables required for cohort derivation and risk adjustment. Data will not be patient identifiable. The full data specification can be found in Additional file 2.

Baseline data extracts will be requested from the 20 randomised units covering 1 year prior to the start of the OASI2 implementation period. For the ten units in the sustainability arm, baseline data extracts will cover the time period between end of the OASI1 study and start of OASI2. All subsequent data extracts during the implementation period will be requested quarterly to enable the Project Team to monitor the quality of the data extracts and to resolve any data-related queries early on. During the implementation period, clinicians will be asked to record their use of (or compliance with) the OASI-CB for every vaginal birth they attend. At minimum, this will be a single yes/no question: ‘were all four components of the OASI-CB applied to this birth?’ Where possible, a field will be added to the local MIS to facilitate collection of these data.

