#### Women’s postnatal surveys

Women who give birth in participating units will be surveyed about their experiences with the OASI-CB. Survey questions have been extensively reviewed by patient and public involvement (PPI) groups for sensitivity. Over a 4-month period, all women who had a live vaginal birth will be invited to participate in the survey by way of a census method. An attending clinician will approach eligible women at an appropriate time after birth and before discharge from the hospital to explain the survey and provide a participant information sheet and consent form. Participants will receive a link to the online survey via e-mail 2 weeks after the birth of their baby and up to three reminders thereafter if the survey has not yet been completed. Assuming a 30% response rate [29, 30], an estimated 8000 surveys will be completed, which is adequate for descriptive analyses (no comparators for these survey data).

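### The cluster size of 3600 appears to count all births, but OASI is analysed in vaginal births only; on the plan's own survey forecast, power would be roughly 62–72% rather than 80%

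*Protocol article*

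**What the plan says.** The Sample size and power section seeks the smallest number of units "to provide a study power of at least 0.80 with a statistical significance level of 0.05", in order "to detect a 0.5% difference in OASI rates between the peer support and lean implementation arms". The assumed rates after implementation are 2.8% (peer support, a 20% relative reduction from 3.5%) and 3.3% (lean, a 5% relative reduction). The other inputs are a baseline period, cross-sectional sampling, an exchangeable correlation structure, an intraclass correlation of 0.007, a coefficient of variation of cluster size of 0.4, and "a cluster size of 3600 (average maternity unit size according to NMPA"). The result is ten units per arm.

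The analysed population is narrower. Under Data collection and management (Clinical effectiveness evaluation), "All women who have a vaginal birth (spontaneous or assisted) are eligible to receive the OASI-CB", with exceptions for non-consent and for unsuitable birthing positions. The Data analysis section calculates OASI rates among eligible women. The Background describes OASI as a complication of vaginal childbirth.

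Women's postnatal surveys invites all women with a live vaginal birth over four months and, at 30% response, expects that "an estimated 8000 surveys will be completed, which is adequate for descriptive analyses".

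**The concern.** The article gives unit size in one other place: Study participants matches candidate units on their yearly number of births, with no restriction to vaginal births. Read the same way, 3600 includes caesarean births, which cannot contribute to the OASI rate. Each analysis period lasts about a year (one year of baseline data and a 12-month implementation period), so a longer period does not make up the gap.

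This figure sets the number of clusters for the primary effectiveness comparison. If it is too large, the chance of missing the assumed difference between peer support and lean implementation is nearer one in three than the one in five stated. That matters for reading a non-significant result in a trial meant to inform national scale-up.

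**Working it through.** **1. Vaginal births implied by the survey forecast.** Inputs: 8000 completed surveys, 30% response and 4 months (Women's postnatal surveys); 30 units (Study participants).

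- 8000 / 0.30 = 26,667 women in 4 months.
- 26,667 / 30 × 3 = 2,667 per unit-year, which is 2,667 / 3600 = 74% of 3600.
- In reverse, 3600 vaginal births per unit-year would give 3600 × 30 × 4/12 × 0.30 = 10,800 completed surveys, not 8000.

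**2. Variance formula.** For a two-period parallel cluster trial with cross-sectional sampling, exchangeable correlation, k units per arm and m women per unit-period, under a linear mixed model:

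- s² = mean of p(1−p) over the arms; τ² = ICC × s²; e = (1 − ICC) × s² / m; r = τ² / (τ² + e)
- Var = (2/k) × e × (1 + r)
- Power (z test, two-sided 0.05) = Φ(d/SE − 1.96)

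The formula assumes equal unit sizes. Repeating the calculation with gamma-distributed sizes (coefficient of variation 0.4) leaves power unchanged to three decimals. The article does not state sidedness; two-sided is assumed.

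**3. Reproducing the plan: m = 3600, k = 10, 3.3% vs 2.8%.**

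- s² = (0.033 × 0.967 + 0.028 × 0.972)/2 = 0.02956; τ² = 0.000207; e = 0.02936/3600 = 8.15 × 10⁻⁶; r = 0.962
- Var = 0.2 × 8.15 × 10⁻⁶ × 1.962 = 3.20 × 10⁻⁶; SE = 0.00179
- Power = Φ(0.005/0.00179 − 1.96) = 79.8%

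This matches the stated 0.80. Reading 3600 as the total over both periods (1800 each) gives 51%, so 3600 per period is evidently what was used.

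**4. The same calculation with m = 2,667.**

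- e = 1.10 × 10⁻⁵; r = 0.950; Var = 0.2 × 1.10 × 10⁻⁵ × 1.950 = 4.29 × 10⁻⁶; SE = 0.00207
- Power = Φ(0.005/0.00207 − 1.96) = 67.5%

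**5. Variants, ten units per arm.** The unrounded lean rate is 3.5% × 0.95 = 3.325%.

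| Women per unit-period | z, 3.3% vs 2.8% | z, 3.325% vs 2.8% | t (18 df), 3.3% vs 2.8% | t (18 df), 3.325% vs 2.8% |
|---|---|---|---|---|
| 3600 | 79.8% | 83.4% | 75.2% | 79.1% |
| 3,000 | 72% | 76% | – | – |
| 2,667 | 67.5% | 71.5% | 62.1% | 66.3% |

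**6. Difference detectable with 80% power (z test).** (1.96 + 0.84) × SE: 2.80 × 0.00179 = 0.50 percentage points at 3600, and 2.80 × 0.00207 = 0.58 at 2,667.

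**The case against.** The article does not say outright that 3600 counts all births, and the audit it cites is not at hand. The reading rests on the label, on how unit size is measured elsewhere, and on the survey arithmetic.

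The 2,667 is not a planning figure either. It is worked back from a rounded forecast whose derivation is not shown. Women must be approached before discharge and consent, so 8000 may already allow for some who are missed. If 8000 / 10,800 = 74% of eligible women were approached and consented, the forecast would fit 3600 vaginal births. At 8000 / 9,000 = 89% it would fit 3,000. A reader might infer that the two figures flatly contradict each other; that holds only if no such allowance was made.

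The vaginal births in OASI1 (55,060 / 16 = 3,441 per unit) do not settle the matter, because the accrual time per unit is not given.

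Nothing was miscalculated: the stated inputs give the stated result. The number of units, the analysis model and the eventual estimate with its interval are unaffected, and nothing in the article says that a non-significant result will be read as equivalence. All of this stands. It limits how firmly the shortfall can be stated, but it does not remove the unexplained step between unit size and the women analysed.

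**Conclusion.** The concern holds in conditional form. The power calculation very probably uses a denominator wider than the one analysed. If vaginal births per unit-year are about 2,670, power with ten units per arm is roughly 62–72%: about 67% for 2.8% vs 3.3% and about 71% for 2.8% vs 3.325% by z test, with t tests on 18 degrees of freedom giving the lower values. At 3,000 vaginal births per unit it is about 72–76% (z test).

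These figures assume that 3600 counts all births, that all 30 units join the survey, and that the 30% response applies to every eligible woman. The other inputs are taken as stated. A reader might go further and give a single corrected power, such as 66%, or call this an arithmetical error. The documents support neither: the denominator is inferred, and the plan's calculation reproduces on its own inputs.

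**What to change.** In the Sample size and power section, state what 3600 counts. If it is all births, rerun the calculation with the expected number of vaginal births per unit per 12-month period. The actual baseline counts of the 20 randomised units are preferable to the figure worked back from the survey. Keep ten units per arm, and restate either the power for the assumed difference or the difference detectable with 80% power (about 0.58 percentage points at 2,667). Say whether 3.3% or 3.325% was used. If 3600 was meant as vaginal births, say so and reconcile it with the 8000 in Women's postnatal surveys, for instance by stating the allowance for women not approached.

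The cost is one paragraph of wording and one rerun, using baseline data that will be extracted anyway. No units are added and the analysis does not change. The stated power will probably be less favourable.

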### Clinical effectiveness evaluation

#### Data collection and management

The clinical effectiveness of the OASI-CB is evaluated through its impact on perineal outcomes in women across all participating units. As OASI is an acute pregnancy outcome, women may receive the four elements of the bundle as they become eligible, dependent on whether the attending clinician (midwife or obstetrician) chooses to, or is trained to use the care bundle. Women are not randomised to receive the care bundle. All women who have a vaginal birth (spontaneous or assisted) are eligible to receive the OASI-CB, unless they do not consent to one of the elements of the care bundle or are in a birthing position that makes it unfeasible to implement all elements of the care bundle (e.g. water birth).

Individual woman-level data will be extracted from local electronic Maternity Information Systems (MIS) for all participating units in England, Scotland and Wales. The MIS data extract will include demographic and clinical information related to primary and secondary clinical outcomes, as well as a small set of variables required for cohort derivation and risk adjustment. Data will not be patient identifiable. The full data specification can be found in Additional file 2.

Baseline data extracts will be requested from the 20 randomised units covering 1 year prior to the start of the OASI2 implementation period. For the ten units in the sustainability arm, baseline data extracts will cover the time period between end of the OASI1 study and start of OASI2. All subsequent data extracts during the implementation period will be requested quarterly to enable the Project Team to monitor the quality of the data extracts and to resolve any data-related queries early on. During the implementation period, clinicians will be asked to record their use of (or compliance with) the OASI-CB for every vaginal birth they attend. At minimum, this will be a single yes/no question: ‘were all four components of the OASI-CB applied to this birth?’ Where possible, a field will be added to the local MIS to facilitate collection of these data.

Data from each unit will be cleaned and re-coded to ensure consistent definitions for all variables. Data quality will be assessed by checking data completeness, plausible distributions and internal consistency. Multiple imputation methods (e.g. statistical coefficients obtained from ten imputed data sets pooled using Rubin’s rules [26]) will be used to deal with missing data, if possible, following an assessment of the extent and patterns of missing data. Plausible distribution checks include assessing whether the distributions calculated from non-missing data is within a clinically possible and acceptable range (e.g. OASI rates less than 15%). Internal consistency checks include assessing agreement of data that might be present in more than one data field (i.e. repair of a tear would only be recorded in women who had an OASI). Any implausible distributions or high levels of internal inconsistency would suggest data extraction errors or systematic errors in coding, which would need to be discussed with the unit’s MIS team, and a new revised extract will be requested if required.

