#### Data analysis

Routine data extracted from the MIS will be first analysed descriptively, with OASI rates, caesarean birth rates, episiotomy rates and OASI-CB use calculated for all eligible women pre and post implementation and by study arms. Because units in the sustainability arm have already implemented the OASI-CB as part of OASI1, effectiveness outcomes in these units will be analysed differently than in the two C-RCT arms.

For the C-RCT arms, multilevel logistic regression and estimation of adjusted odds ratios (aOR) will be used to assess the impact of the OASI-CB and the relative differences in the odds of OASI in the two C-RCT arms. The regression model will include a random effect to account for clustering at unit level, secular trends and individual case-mix factors (e.g. maternal age, ethnicity, BMI, parity, mode of birth and birthweight).

For the sustainability arm, OASI rates will be analysed longitudinally from the baseline period of OASI1 to end of OASI2, to ascertain the trends and the rate of change by various implementation strategies. The four specific time periods will include baseline (pre-OASI1), OASI1 implementation, post-OASI1 with no external support and OASI2. We will use multilevel logistic regression with random effects and case-mix adjustment as in the C-RCT arms, to estimate adjusted odds ratios (aOR) for each time period and to test the significance of the relative impact of OASI1 implementation as compared with OASI2 implementation to assess the effectiveness of additional “sustainability” strategies.

For all study arms, subgroup analyses of the effect of the care bundle on OASI rates will be carried out according to mode of birth (spontaneous or assisted) and parity. The Wald test will be used to test for significance of interaction terms.

The analysis will be done following intention-to-treat principle, with births analysed according to whether they took place during the baseline or implementation periods, irrespective of whether or not all aspects of the care bundle could be implemented.

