### Synthesis of clinical effectiveness and implementation data

If compliance (clinicians’ use of the OASI-CB) and survey data are of sufficient completeness and quality, this unit level data will be added to multivariate regression models with effectiveness data to identify and estimate any relationship between OASI rates and levels of OASI-CB adoption as well as any secondary implementation outcomes. For the two C-RCT arms, the regression analysis will assess the impact of care bundle adoption (based on NoMAD score from clinicians’ survey) on relative differences of odds of OASI. In the sustainability arm, the regression analysis will assess the impact of additional ‘sustainability strategies’ on the adoption of the care bundle and on odds of OASI.

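### The minimum bundle-use item gives the same 'no' to clinician non-use and to births the protocol calls not eligible, and pre-implementation use has no stated source in the sustainability arm

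*Protocol article*

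**What the plan says.** All references are to the protocol article.

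- **What is recorded, and when** (*Data collection and management*): in the implementation period, "clinicians will be asked to record their use of (or compliance with) the OASI-CB for every vaginal birth they attend". The form is a floor: "At minimum, this will be a single yes/no question: ‘were all four components of the OASI-CB applied to this birth". Storage depends on the local system: "Where possible, a field will be added to the local MIS to facilitate collection of these data".
- **Who is eligible for the bundle** (same section): every woman with a vaginal birth, "unless they do not consent to one of the elements of the care bundle or are in a birthing position that makes it unfeasible". Water birth is the example given.
- **What is to be summarised** (*Data analysis*): "OASI-CB use calculated for all eligible women pre and post implementation and by study arms". The same phrase also governs OASI, caesarean and episiotomy rates.
- **How it is used later** (*Synthesis of clinical effectiveness and implementation data*): compliance is glossed as use of the bundle by clinicians. If it and the survey data are complete and good enough, "this unit level data will be added to multivariate regression models with effectiveness data".
- **Baseline windows** (*Data collection and management*): one year before implementation for the 20 randomised units; from the end of OASI1 to the start of OASI2 for the ten sustainability units.

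**The concern.** The item is asked at every vaginal birth, but the protocol's own eligibility rule removes some of those births from the group that could receive the full bundle. For them the only truthful answer is 'no', which is also the answer for an eligible woman whose clinician did not use the bundle or used only part of it. A figure described as use by clinicians would then partly reflect how many women declined an element or gave birth in a position that ruled the bundle out. *Evaluation framework and study outcomes* also assesses how widely clinicians offer the bundle; a woman who was offered it and declined would count as a failure.

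The second mismatch is one of timing. The summary is to cover the periods before and after implementation, but recording is described for one period only. At stake are the comparison of bundle use across units and arms, any statement about change in use, and the interpretation of the models relating compliance to OASI.

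**Working it through.** The protocol states no rate of bundle use and no share of declined or unfeasible births, so there is no figure to reproduce. The check sets the sections side by side, with an illustration on assumed values.

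**1. What the minimum item identifies.** Let *x* be the share of vaginal births where an element was declined or the position made the bundle unfeasible, and *u* the share of the remaining (eligible) births in which all four components were applied. A birth in the first group cannot be a truthful 'yes', so the recorded share is

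R = u × (1 − x), and hence u = R / (1 − x).

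R alone does not give *u*; *x* is also needed, and the minimum item does not record it.

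**2. Size, on assumed values.**

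| Assumed x | Recorded R if u = 80% | True u if R = 60% |
|---|---|---|
| 0% | 80% | 60% |
| 5% | 0.80 × 0.95 = 76% | 0.60 / 0.95 = 63% |
| 10% | 0.80 × 0.90 = 72% | 0.60 / 0.90 = 67% |
| 20% | 0.80 × 0.80 = 64% | 0.60 / 0.80 = 75% |
| 30% | 0.80 × 0.70 = 56% | 0.60 / 0.70 = 86% |

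Where *u* is equal, the recorded gap between two units or arms is u × (x₂ − x₁). With u = 80%, shares of 10% and 20% give 0.80 × 0.10 = 8 points; shares of 5% and 25% give 0.80 × 0.20 = 16 points (76% against 60%). Recorded use also cannot exceed 1 − x, which is 95% and 75% in the last case.

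**3. What a third answer would recover.** Take the 5% and 25% units, per 100 vaginal births and with u = 80%:

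- First unit: 76 yes, 19 no although eligible, 5 declined or not feasible. Use among eligible births is 76 / (76 + 19) = 80%; over all births it is 76%.
- Second unit: 60 yes, 15 no although eligible, 25 declined or not feasible. Use among eligible births is 60 / (60 + 15) = 80%; over all births it is 60%.

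Both measures become available, and the reason that they differ is visible.

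**4. Before and after.** Recording is described for the implementation period only. *Background* describes the randomised units as implementing the bundle for the first time, so their baseline use can be taken as about zero, though it is not measured. The sustainability units' baseline window begins after OASI1 had introduced the bundle, so zero cannot be assumed there, and no source for that period's use is named.

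**5. What depends on the item.** The OASI analysis classifies births by period whether or not the bundle could be applied (*Data analysis*). Adoption is measured with NoMAD (*Clinicians' survey*). Neither uses this item. The descriptive use summary does, and so do the synthesis models if compliance is entered.

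**The case against.** A reader might infer that bundle use cannot be calculated at all, or that the trial's comparison is compromised. The documents do not support either reading.

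- **The single question is a minimum.** Fuller recording is left open. This stands, but the floor is all that the protocol guarantees, and if some units record more than others, only the yes/no is comparable across all of them.
- **'Eligible women' in *Data analysis* may mean the analysis cohort.** The phrase also covers caesarean rates, which cannot be calculated among women defined by having a vaginal birth. On that reading, the share of all vaginal births with the full bundle is coherent. So a contradiction over the denominator is not proven; what stands is that the item cannot isolate clinicians' use, which is how the synthesis section describes it.
- **The data specification is in Additional file 2, which is not shown.** It may identify water births. It might not capture refusal of an element, which is a separate ground for ineligibility. Neither can be verified here.
- **First-time units need no measured baseline.** This stands. The real gap is in the sustainability arm.
- **The synthesis models are conditional, and the adoption measure named there for the randomised arms is NoMAD.** This stands and limits the consequence. Even so, a fully completed yes/no field could meet a completeness test and still mix the reasons for 'no'.
- **No systematic gap between the randomised arms is to be expected.** Units were shortlisted as similar in type and annual births and then randomised within pairs. This stands for systematic differences; it does not exclude chance differences across ten pairs, or differences between units or from the non-randomised arm.
- **Use among eligible births is not clearly the better predictor.** A unit's OASI rate over all vaginal births depends on the share of all births that received the bundle. This stands: the choice of denominator in the synthesis models should be stated, not presumed.

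**Conclusion.** The concern holds in a limited form. If only the minimum item is collected, a 'no' does not separate clinician non-use from births that the protocol itself calls not eligible, so recorded use understates use among eligible women by a factor of 1 − x that the item does not reveal and that may differ between units. On assumed shares of 0% to 30%, a recorded 60% is compatible with true use of 60% to 86%. These figures show the mechanism only; the documents give no shares. Separately, use before implementation is planned without a stated source, which matters in the sustainability arm.

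The effect is confined to the descriptive summary of bundle use and the conditional synthesis models. The primary OASI comparison and NoMAD adoption stand as planned. The point is still worth settling before data collection, because eligibility not recorded at the birth cannot reliably be recovered later.

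**What to change.** 1. In *Data collection and management*, make the minimum item three-way: yes; no, although eligible; declined or not feasible.
2. In *Data analysis*, report bundle use over all vaginal births and over eligible births, with the declined or not-feasible share by unit and arm.
3. In the synthesis section, state which denominator enters the models and run the other as a sensitivity analysis.
4. Limit the bundle-use summary to the implementation period, or name a source for baseline use in the sustainability arm.
5. Keep all vaginal births in the OASI analysis, as planned.

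The cost is one extra response option and a few lines of analysis text. The downside is small: clinicians may over-use the third answer, which the separate report by unit and arm would show.
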